## DESIGN AND PROCESS OF INTRODUCING PREP DELIVERY IN FP CLINICS

Systematic integrated screening for HIV risk and counseling for and provision of PrEP will be introduced and actively promoted in family planning clinics in Kisumu. These strategies will be introduced in staged three successive waves (steps), occurring every 3 months, with 4 clinics per step or stepped-wedge design (**Figure 2**). The order at which clinics initiate the implementation will be determined

[figure not shown]

by randomization stratified by clinic size, identified as likely to have a marked effect on implementation outcome. Randomization process will take place at a meeting with the Kisumu County Health leadership, implementing health facilities and led by the project staff. Prior to initiating implementation of the program, we will conduct clinic-wide training for health providers at each clinic and we will engage existing FP providers in continuous quality improvement to optimize delivery. At all implementing clinics, we will conduct a pre-implementation needs assessment and observation of current services to optimize data and PrEP supply systems. During this pre-implementation period, a minimum of 3 months for each clinic, we will assess and document current processes on HIV counseling and testing, male partner testing, PrEP counseling and use (expected to be minimal), STI counseling and treatment, male partner STI testing and treatment of women infected with STIs, incident HIV and STI. During implementation, we will optimize delivery of PrEP in combination HIV prevention using existing FP clinic staff supported through ongoing technical assistance from program technical team and MOH/NASCOP and Kisumu County Health supervision team to audit for process indicators of implementation progress and continuation quality improvement. On-the-job training of new staff will be promoted and we will conduct refresher CME-like training quarterly or as needed.

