| Target of action | Health providers in FP clinics                                                                                              | Health providers in FP clinics                                                                                                        | Clinic manager/ Health providers in FP clinics                                    | FP clinics/clinic staff                                                                                       | FP clinic systems/Clinic managers                                                                 |
| Temporality      | 2-4 week prior to implementation                                                                                            | Baseline                                                                                                                              | Implementation                                                                    | Baseline                                                                                                      | Baseline                                                                                          |
| Frequency        | MOH PrEP curriculum delivered in 5 modules over 2 weeks at the facility premises. Ongoing refresher 3-6 months or as needed | Weekly TA visits for 6 months, then monthly for 6 months. 3 monthly with study nurse for 18 months then 3 monthly alone for 6 months. | 2 weekly for 3 months, then monthly for 9 months                                  | At baseline, 6, and 12 months                                                                                 | Baseline, then ongoing and fully optimized within 12 months.                                      |
| Outcomes         | # of providers trained, provider knowledge gain, confidence to deliver PrEP                                                 | Fidelity, Maintenance (sustainability)                                                                                                |                                                                                   | Adaptations to clinic flow. Client time in clinic, provider time spent to provide services. PrEP continuation | Data and M & E tools completeness PrEP commodity stock out                                        |

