PrEP technical assistance and county supervision: We will conduct ongoing technical assistance to clinics using trained program nurses to coach, mentor, and guide FP clinics to troubleshoot emerging challenges with integrating new services. Technical advisors (TA) will be project nurses with training in PrEP delivery. Prior to implementation, Program nurses will undergo an intensive 2 weeks didactic and protocol training conducted by study investigators, in collaboration with Kenya MOH and Kisumu Health officials. TA will conduct structured periodic visits to each clinic to coach and mentor the health care providers and observe and document PrEP implementation processes with a specific focus on processes that are effective or not and aspects of delivery that are changing with time. Using rapid-cycle analysis approaches, TAs will make summary reports at the end of each clinic visit highlighting what changed, why it changed, who initiated the changes, and outcome of any changes instituted. Best practices will be shared across all clinics for possible adoption. For the first 3 months post-introduction, study nurses (TAs) will visit clinics weekly for 3 months, and then complete monthly visits through the 12-month intensive implementation phase. During year 2, TA activities will scale back to observe sustainment phase. Throughout the first 18 months, the TAs will be accompanied to facility visits by County health and or Kenya MOH/NASCOP supervisors to audit for process indicators for FP services, HIV prevention services, and PrEP and progress.

Novel clinic and patient flow mapping: We will conduct workflow mapping at all sites to identify potential bottlenecks, differences and commonalities among sites at baseline and 6 monthly. We will solicit provider engagement in defining new flow maps to accommodate new tasks and patient flows. Current and future flow maps will be created for each site to demonstrate new pathways.

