periods of intensive care in baseline and steps 1-3 to estimate a relative risk (RR) for the outcome associated with implementation. We will estimate each RR using a generalized mixed model. The key predictor will be intervention status of the clinic during the step in which the participant is enrolled, as a fixed effect. The model will also include step, as a fixed effect, and clinic, as a random effect. The model may also include a random effect for step and for the intervention effect, if evidence in our data shows that these are in fact varying randomly and not fixed. The mixed model will generate RRs using a modified Poisson model (i.e. Poisson regression with robust error variance) with robust standard errors to allow valid estimation of SEs for log (RR) from Poisson regression, which is a very stable model compared to alternatives. Using Steps 3-4 vs 7-8 (see **Figure 2**), we will conduct secondary analyses using similar methods to estimate changes in outcome during the maintenance phase compared to the intensive phase to quantitatively ascertain level of institutionalization. We will also describe, over the steps, the proportion of clients screened for HIV prevention including HIV testing and PrEP counseling, to assure that the intervention is being implemented as expected and ensure that any increase in % screening for HIV risk observed, includes PrEP counseling as part of the standard package now reaching a larger proportion of women. For individual level data from open-cohort, descriptive analyses will be done at baseline and over time, and appropriate regression models (e.g., cox proportional hazards for survival outcomes, and generalized estimating equation for binary or count data) comparing clinical outcomes between women who initiated PrEP vs those who chose not to initiate PrEP, accounting for age, partner HIV status, repeated measures, time-dependent exposures, and clinic-clustering.

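### The primary model gives one effect for all lengths of exposure; if the effect changes with time since start, the reported RR is not its average, so exposure-specific effects should be prespecified beside it

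*Protocol*

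**What the plan says.** The protocol's design section has the strategy "introduced in staged three successive waves (steps), occurring every 3 months, with 4 clinics per step". The paragraph on analysis of quantitative data (DATA section) compares usual-care with intervention periods over baseline and steps 1-3, and defines the treatment term: "The key predictor will be intervention status of the clinic during the step in which the participant is enrolled, as a fixed effect". It goes on: "The model will also include step, as a fixed effect, and clinic, as a random effect". A further option is data-dependent: "The model may also include a random effect for step and for the intervention effect, if evidence in our data shows" that they vary. No term for time since a clinic started is named. The only other time-related comparison is secondary, between steps 3-4 and steps 7-8.

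Elsewhere delivery is described as developing. Table 3 gives the frequency for data and PrEP supply systems as "Baseline, then ongoing and fully optimized within 12 months" and schedules audit and feedback over 12 months. The paragraph on technical assistance says that the advisers "complete monthly visits through the 12-month intensive implementation phase" and asks them to document "aspects of delivery that are changing with time".

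**The concern.** In the primary window the first wave of clinics has at most three steps of exposure, or 9 months, which ends before the 12-month limit in Table 3. A single on/off term treats months 1-3, 4-6 and 7-9 after start as interchangeable. In a stepped wedge this matters more than in a parallel trial. Clinics that switch late are compared partly with clinics that switched earlier, so any further growth in the early clinics is absorbed into the step effects and subtracted from the intervention effect.

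Both co-primary outcomes, screening and PrEP initiation, use this model. The health economics section then takes intervention effectiveness as an input to cost per HIV case averted and to budget impact. A distorted RR would carry through to those figures.

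**Working it through.** **Inputs from the protocol.** 12 clinics in three waves of four; four periods, so the on/off patterns are 0111, 0011 and 0001. Screening: 3,600 women = 12 x 4 x 75, 50% to 60%, two-sided 0.05, stated power 83.8% (Table 2). PrEP: 4,800 = 12 x 4 x 100, baseline below 2%, expected +20 points.

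**Assumed, because no ICC or variance component is given.** Clinic SD (tau) and SD of the intervention effect between clinics (eta).

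**Reproducing the stated power.** Cell-mean generalised least squares with V = (sigma²/m)I + tau²J + eta²xx', sigma² = p(1-p) at the mid-point proportion, and power = Φ(δ/SE - 1.96). With tau = 0.10 and eta = 0.05, the SE for 50% to 60% at m = 75 is 0.034. Power is Φ(0.10/0.034 - 1.96) = 83.6%, against the stated 83.8%. The other five screening entries agree within 1 point. With tau = eta = 0 the power would be 98%, so Table 2 does allow for clustering.

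**Weights on exposure steps 1, 2 and 3.** These are the treatment row of (ΣX'V⁻¹X)⁻¹ΣX'V⁻¹Z, where Z holds the exposure-step indicators. Two limits can be checked by hand:

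- *No clinic variance.* Only within-step contrasts count. Step 1 compares 4 clinics on with 8 off (information 4 x 8/12), and step 2 compares 8 on with 4 off (the same). In step 3 all clinics are on, so it adds nothing. Step 1 is all first-step exposure; step 2 is half first and half second. Weights: 0.5 + 0.25 = **0.75**, **0.25**, **0**.
- *Large clinic variance.* Remove wave and step means from the on/off pattern. The residuals in treated cells sum to 1.000 for exposure 1 (0.417 + 0.333 + 0.250), 0.083 for exposure 2 (0.083 + 0) and -0.250 for exposure 3; the total is 0.833. Weights: **1.20**, **0.10**, **-0.30**.

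Screening (tau 0.10, eta 0.05, m = 75): 1.166, 0.107, -0.273. More women do not help: at 337 per clinic-step they are 1.20, 0.09, -0.29.

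| Assumed true effects (points) | True average | Target of the on/off model |
|---|---|---|
| 10 / 10 / 10 | 10 | 10.0 |
| 8 / 10 / 12 | 10 | 1.166x8 + 0.107x10 - 0.273x12 = 7.1 |
| 5 / 10 / 15 | 10 | 1.166x5 + 0.107x10 - 0.273x15 = 2.8 |
| 15 / 10 / 5 | 10 | 17.2 |

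PrEP (2% to 22%, m = 100, clinic SD 1.2 points, separate binomial variances before and after start):

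- eta = 0: weights 0.73, 0.30, -0.03; +10/+20/+30 is estimated as +12.4.
- eta = 5 points: weights 0.94, 0.23, -0.17; the same pattern is estimated as +8.9.
- With one pooled binomial variance instead, the two figures are +10.6 and +6.8.

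**RR scale.** A Poisson mixed model was fitted to 300 simulated data sets per scenario. True RRs of 1.1/1.2/1.3 gave about 1.06 to 1.10, and 6/11/16 gave about 3.8 to 4.2. Constant RRs of 1.2 and 11 were recovered as 1.19 and 11.2.

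**Cost of averaging three exposure-specific effects.** Screening at m = 75: SE 0.053 against 0.034 (ratio 1.56), so power for 50% to 60% falls from 84% to 47%. At m = 231 it is 77% and at m = 337 it is 86%. For PrEP the SE ratio is about 1.3 to 1.5, and power for +20 points stays above 99%. The 231 is 25,000/(12 x 9); the 337 is Table 1's 1,348 new visits a month x 3/12.

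**The case against.** The strongest reply is that the protocol never says the effect on screening or PrEP initiation grows. The 12-month wording concerns one column of Table 3 (data and supply systems), and it sets an upper limit. The remark on delivery changing with time tells advisers what to record and gives no direction. Other text points to an early effect: training finishes just before start, supply is prepared during a pre-implementation period of at least 3 months, and support visits are most frequent at first (weekly for 6 months in Table 3, for 3 months in the text). All of this stands. A constant effect is an unsupported assumption here, not a contradiction of the protocol, and the growth patterns above are illustrations.

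It is also fair that mild trends cost less (+8/+10/+12 loses about 3 points, +5/+10/+15 about 7), and that an SAP, not shown, could add exposure-time terms. But the protocol itself fixes the treatment term. The optional random intervention effect describes variation between clinics, so it does not remove the negative weight. The steps 3-4 versus 7-8 comparison leaves the primary estimate as it is, and describing screening step by step gives no exposure-specific RR.

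The power cost of the alternative is real: 47% for 50% to 60% at the stated 3,600 women. The larger numbers per clinic-step rest on a ceiling of 25,000 records over nine periods, or on potential sites whose new visits range from 34 to 351 a month. Conversely, under +5/+10/+15 the on/off test itself has only about 13% power at 75 women per clinic-step. Neither model is better in every case.

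**Conclusion.** The point holds as a conditional one. The planned estimate equals the average effect only if the effect does not depend on time since start. Otherwise most of the weight falls on the first step (about 0.7 to 1.2 across the settings tried), and the third step gets a weight between 0 and about -0.3. For screening, growth from +8 to +12 would be reported as about +7, and from +5 to +15 as about +3. For PrEP, +10/+20/+30 would be reported as about +9 to +12, somewhat less with a pooled binomial variance. These sizes rest on assumed variance components and assumed patterns. With no effect at any exposure there is no bias, so the on/off model remains a valid test.

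Four stronger readings are not supported:

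- A reader might infer that the protocol predicts a rising effect. It does not. Its 10% to 30% range for PrEP is spread between clinics, not over time.
- Applying a clinic SD of 10 points to PrEP would give a figure below +6, but that SD does not fit a baseline of 0-5% across clinics.
- The screening estimate would not be falsely precise: 2.8 ± 1.96 x 3.4 runs from about -3.9 to +9.5.
- The exposure-averaged estimate should not become the headline test, given its power at 3,600 women.

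**What to change.** In the paragraph on analysis of quantitative data, keep the on/off model as the primary test. Add one prespecified key supporting analysis for both co-primary outcomes: the same step fixed effects and clinic random effect, with the single term replaced by separate indicators for a clinic's first, second and third step since start. Report the three exposure-specific RRs and their average beside the primary RR. State that, if the two differ, claims about effect size and the inputs to the economic models will draw on both.

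The cost is analysis wording and programming; no new data are needed. The drawback to state openly is lower precision: an SE about 1.3 to 1.6 times larger, with power for 50% to 60% screening of about 47% at 3,600 women and about 77% to 86% only if 231 to 337 women per clinic-step are available. The third-step effect is the least certain, because only the four first-wave clinics reach it within the window.

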**Sample size and power:** For this facility-level intervention, the co-primary outcomes will be: 1) proportion of women accessing FP services that are counseled and screened for HIV risk, and 2) proportion of women who initiate PrEP. HIV testing is the entry point for all HIV services. Although HIV counseling and testing an expected service in FP clinics, it is not routinely done in most FP settings. Assuming a conservative 50% rate in the current practice, with 3600 total women screened, we will have  $\geq 80\%$  power to detect a meaningful increase of 10% or more in proportion of new clients screened for HIV prevention. We assume the average proportion being screened at project start will be between 50% and 70%, accounting for heterogeneity in baseline levels and treatment effect, we will have  $\geq 80\%$  for the range of likely baseline levels of screening. We expect that prior to starting the intervention, PrEP initiation will be very low, averaging  $<2\%$  (ranging from 0-5% across clinics). After the intervention, we expect to see PrEP initiation among general population women increase to a mean of 22% (based on preliminary work, [name] et al *PLOS Med* 2019), much higher among women with risk factors for HIV. Sample size and power calculations for stepped wedge cluster randomized trials should account for possible heterogeneity in intervention effects so that the study is not underpowered. We expect that the overall increase of +20% will reflect a range of true intervention effects across clinics depending on clinic factors, likely distributed between 10%-30%. Accounting for heterogeneity in baseline levels and intervention effect, if each clinic offers universal counseling for HIV risk and offer of PrEP for at least 100 new women per step, totaling at least 4800 new women overall, using a two-sided  $\alpha=0.05$ , the study will have excellent power to detect the expected increase in PrEP initiation (**Table 2**). To fully understand how public health clinics build new efficient systems for delivery of integrated FP and HIV prevention services, we will abstract data on all HIV-uninfected women accessingservices in implementing clinics in order to establish the underlying denominator in the program. Based on data from the baseline preparatory periods (monthly volume of ~1000) and a conservative PrEP screening rate between 10-30%, we estimate that program data on up to 25000 women accessing services across the 12 FP clinics will be needed for thorough evaluation of this new program beyond the statistical sample size. This sample size will permit a full-scale test of the system, since the efficiency in delivery is in large part at the system level, above and beyond the individual client encounter.

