
**Table 2: Power to detect an increase of 10-15% in counseled and screened for HIV risk in stepped wedge design with 12 clinics and 3 steps.**

| Total clients in study                                                                                                                | Effect size            | % new clients screened for HIV prevention |                                      |           |      |      |
|---------------------------------------------------------------------------------------------------------------------------------------|------------------------|-------------------------------------------|--------------------------------------|-----------|------|------|
|                                                                                                                                       |                        | Current practice                          | Intervention                         | Power (%) |      |      |
| 3,600                                                                                                                                 | 10%                    | 50%                                       | 60%                                  | 83.8%     |      |      |
|                                                                                                                                       |                        | 60%                                       | 70%                                  | 86.2%     |      |      |
|                                                                                                                                       |                        | 70%                                       | 80%                                  | 90.8%     |      |      |
|                                                                                                                                       | 15%                    | 50%                                       | 65%                                  | 98.8%     |      |      |
|                                                                                                                                       |                        | 60%                                       | 75%                                  | 99.2%     |      |      |

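### Robust standard errors on 12 clinics do not secure the stated two-sided 5% level unless a small-sample correction and reference distribution are fixed

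*Protocol*

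**What the plan says.** The design introduces the programme in "three successive waves (steps), occurring every 3 months, with 4 clinics per step", so 12 clinics form three sequences. The order is set "by randomization stratified by clinic size, identified as likely to have a marked effect on implementation outcome".

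Under DATA, the paragraph on analysis of quantitative data compares usual-care periods with "periods of intensive care in baseline and steps 1-3 to estimate a relative risk (RR"), which makes four periods. The model has intervention status and step as fixed effects and clinic as a random effect. Random effects for step and for the intervention are optional. On the variance: "The mixed model will generate RRs using a modified Poisson model (i.e. Poisson regression with robust error variance) with robust standard errors". The sentence goes on to justify this as giving valid standard errors for the log relative risk from Poisson regression, and cites the modified-Poisson method paper.

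The sample-size paragraph names two co-primary outcomes, screening for HIV risk and PrEP initiation, and states a two-sided alpha of 0.05. Table 2 gives power for screening "in stepped wedge design with 12 clinics and 3 steps", for example 83.8% for 50% to 60% with 3,600 women.

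The protocol does not say at what level the robust variance is clustered, whether it is corrected for few clusters, or which reference distribution applies. It gives no intracluster correlation and no between-clinic or clinic-by-step variance.

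**The concern.** A clinic-level robust (sandwich) variance is built from one contribution per clinic and is justified as the number of clinics grows. With 12 clinics, four period effects and an intervention effect, the fitted residuals are too small. The variance estimate is then biased low and is itself unstable. Unequal clinic sizes make this worse, because a few large clinics dominate.

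Both co-primary p-values and confidence intervals come from this model. If the test rejects more than 5% of the time under no effect, the stated alpha is not delivered and the intervals are too narrow.

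**Working it through.** **Inputs.** From the protocol: 12 clinics, 3 sequences of 4, 4 periods; 75 women per clinic-period for the 3,600 total (3,600 / 48) or 100 for 4,800; baseline screening 50-70%; baseline PrEP initiation below 2% on average (0-5% across clinics); alpha 0.05 two-sided. Table 1 gives 34 to 351 new visits a month, or 91 to 448 attendees counting revisits. Assumed, because not given: clinic SD 0.3-0.6 and clinic-by-period SD 0-0.3 on the logit scale, and intervention-effect SD 0 or 0.3.

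**Step 1: the plan's own figure (83.8% power).** The Hussey-Hughes variance is

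Var = I·s²(s² + Tτ²) / [(IU − W)s² + (U² + ITU − TW − IV)τ²]

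with I = 12, T = 4, U = 24, W = 0² + 4² + 8² + 12² = 224 and V = 4(9 + 4 + 1) = 56. The bracket becomes 64s² + 160τ². For 50% to 60%, s² = 0.55 × 0.45 / 75 = 0.0033 and τ² = ICC × 0.2475.

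- ICC 0.01: Var = 0.000861, SE 0.0293, power Φ(3.41 − 1.96) = 92.6%.
- ICC 0.20: Var = 0.000980, SE 0.0313, power Φ(3.19 − 1.96) = 89.1%.

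The stated 83.8% is lower. Adding a random intervention effect with SD 5 to 6 points gives about 86% to 83%, which brackets it. That agrees with the protocol's statement that heterogeneity was allowed for, but the SD is not given, so the figure cannot be reproduced exactly. Nor does the protocol say whether Table 2 uses a normal or a t reference.

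**Step 2: type I error with a clinic-level robust variance, no correction.** Simulation under no average effect:

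| Model | Clinic sizes | Normal reference | t(10) |
|---|---|---|---|
| Log-Poisson GEE, 5,000-6,000 runs per scenario | equal or Table 1 | 9.8-15.1% (about 10-12% equal, 11-15% Table 1) | 6.3-10.7% |
| Random-intercept Poisson mixed model, 1,500 runs | equal or Table 1 | 11.5-13.3% | 6.3-7.9% (with a 12/11 factor) |
| Poisson with fixed clinic effects, order stratified by size (two strata assumed), 3,000 runs | equal | 9.3-10.4% | 6.0-9.5% (both rows) |
| As above | Table 1 new visits | 11.3-13.1% | as above |

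Monte Carlo standard errors are about 0.4-0.5 points for the GEE and 0.9 for the mixed model. The second row is closest to the stated model. The last two rows show that randomising within size strata does not remove the inflation.

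**Step 3: robust variance over individual women.** Clinic is then handled by the model alone. With clinic indicators standing in for the random effect, 50% baseline and a normal reference, error at 75 / 100 women per cell was:

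| Clinic-by-step SD (assumed) | Type I error |
|---|---|
| 0 points | 5.4% / 5.6% |
| 2 points | 7.2% / 7.2% |
| 3 points | 8.0% / 9.0% |
| 5 points | 15.5% / 16.9% |

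A further run of this kind reached about 18%. The result turns on a variance that the protocol does not give.

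**Step 4: remedies.** GEE with the Mancl-DeRouen correction and t(10) gave 3.0-5.1%; the same correction with a normal reference gave 5.1-7.7%. A permutation test on clinic order gave 4.4-5.4%.

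**Step 5: effect on power.** If Table 2 uses a normal reference (assumption), 83.8% implies a noncentrality of 1.960 + 0.986 = 2.946. Against a t(10) critical value of 2.228, noncentral-t power is 75.7%. By the same route 86.2% becomes 78.5%.

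**The case against.** The strongest reply is that the protocol never says the variance will be uncorrected. It is silent on clustering level, correction and reference distribution, and such details commonly go in a statistical analysis plan, which is not at hand. The validity phrase, read in full, concerns using a Poisson likelihood for a binary outcome and makes no claim about few clusters. Clustering is addressed separately by the random clinic effect, and optional random effects could absorb some clinic-by-step variation. All of this stands.

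A reader might therefore go too far in inferring that the trial's true error rate is 11-16%. The documents do not support that. The rate depends on unstated choices and variances, and ranges from near nominal to about three times nominal.

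Two further inferences are also too strong. New-visit volumes differ about tenfold, but all attendees differ about fivefold (448 / 91 = 4.9), and Table 1 lists potential sites only. Leaving clinic size out of the model matters little, since size is a fixed trait of a clinic and is largely absorbed by the clinic effect.

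The reply does not show that the method as stated holds its level. The robust variance is chosen explicitly, and in its plain clinic-level form it is anti-conservative in every scenario run, across three model forms. A t reference alone does not repair it.

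**Conclusion.** The point holds in conditional form. With 12 clinics, the stated robust-variance analysis does not secure two-sided 0.05. Error is about 9-12% (equal sizes) or 11-15% (Table 1 volumes) if clustered on clinic, uncorrected and referred to the normal; about 6-11% with t(10) alone; and about 5-18% if the variance is over individuals. All these figures rest on assumed between-clinic and clinic-by-step variances.

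The consequence falls mainly on screening, where a 10-point effect is powered at 83.8-90.8%. For the expected 20-point rise in PrEP initiation, Table 2 gives more than 99% power at 75-100 women per clinic-step, so the conclusion is unlikely to change, although the interval could be too narrow. This should be fixed; it does not invalidate the design.

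**What to change.** State in the quantitative analysis paragraph that the robust variance is clustered on clinic, with a named small-sample correction (Mancl-DeRouen, Kauermann-Carroll or Fay-Graubard) and a t reference on about 10 df (12 clinics minus 2) for p-values and confidence intervals of both co-primary outcomes. Of these corrections, only Mancl-DeRouen was checked here.

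A permutation test that re-randomises clinic order within the size strata is an acceptable alternative or sensitivity analysis. There are enough orders for it: with two strata of six clinics (assumed, since the number of strata is not given) there are (6!/(2!·2!·2!))² = 90² = 8,100. In simulation it kept 82-84% power for 50% to 60%. Adding the size stratum as a fixed effect is optional.

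The change costs a sentence or two and some programming, with no extra data. Intervals become wider. If the t reference is adopted, Table 2 should be restated, because the screening power of 83.8% would fall to about 76% if it was computed with a normal reference.
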